### Data management and protection

4.4

The data collected will be stored digitally on data storage devices at the Thoracic Surgery department of the University Medicine Mainz. Data security will be ensured by following the data protection guidelines of the University Medical Center Mainz and complying with legal requirements, including the General Data Protection Regulation (GDPR).

The study will be conducted in accordance with the current version of the Declaration of Helsinki. The study protocol has been approved by the Ethics Committee of the district medical council of Rhineland-Palatinate (approval Nr. 2021–15994). All patient information, including names and other confidential data, will be treated with medical confidentiality and will be subject to the provisions of the State Data Protection Act of Rhineland-Palatinate and the Federal Data Protection Act (LDSG BW and BDSG). Patient data will only be shared in pseudonymized form, and original documents will not be accessible to third parties.

The data will be stored for a period of 25 years, in compliance with the provisions of the Good Clinical Practice (GCP) regulation of August 9, 2004. Participation in the study is voluntary, and patients have the right to withdraw their consent at any time without providing a reason and without any negative impact on their medical care. Before the study commences, participants will be provided with written and verbal information about the nature and scope of the planned investigation, including potential benefits and risks to their health. Their consent will be documented through the signing of an informed consent form. In the event of withdrawal from the study, any data already collected will be destroyed, or the patient will be asked for permission to analyze the existing materials.

## Discussion

5

After thoracic surgery, chest drains are commonly used to facilitate the drainage of fluids and air and provide information about the thorax. However, the conventional chest drain placement can cause discomfort and affect breathing and secretion mobilization, potentially leading to complications such as dystelectasis, atelectasis, or pneumonia.

The smallest drainage diameter is not represented by the lumen of the actual tube, but by the connector diameter. This is the same from 12 Ch to 20 Ch. Therefore, chest drains are divided into two categories based on their sizes: large-lumen (≥20Ch) and small-lumen (≤20Ch) drains.

In a previous experimental study [15], the drainage capacity of a 19F chest drain was compared to a 28F chest drain under both in vivo and in vitro conditions. The study found that the larger-bore drain had a nine-fold increased capacity in vitro, meaning it was able to drain fluid at a much higher rate compared to the smaller-bore drain. However, interestingly, when tested in vivo conditions, both drains demonstrated the same drainage capacity.

Another study [16] focused on the relationship between drain size, fluid viscosity, and flow rate. The study found that there were significant differences in flow rates among catheters with sizes of 8F or smaller, indicating that smaller-bore drains had reduced flow rates compared to larger-bore drains. While large-bore drains offer increased drainage capacity, they are also associated with higher levels of pain. On the other hand, small-bore drains have a higher risk of obstruction or kinking, requiring removal and possible repositioning, which can cause additional discomfort for the patient. Statistically, the risk of obstruction is reported to be 8.1 % with small-bore drains compared with 5.2 % with large-lumen drains [17].

There is currently no standard guideline for managing intraoperative and postoperative drainage after lobectomies due to limited evidence and varying opinions among surgeons [18]. However, the implementation of Enhanced Recovery After Surgery (ERAS) protocols has sparked research focusing on aspects such as the optimal timing of chest drain removal, the number of drains used, the use of suction, and the selection of appropriate drainage systems. Unfortunately, there is a lack of studies specifically dedicated to investigating the impact of drainage lumen size, with limited research available on this topic [[19], [20], [21]].

There is evidence supporting the use of small-bore chest drains in the therapy of empyema, showing equivalent effectiveness compared to large-bore drains [22]. In fact, small-bore, CT- or US- guided drains are currently widely used for the treatment of pleural empyema worldwide. Small-bore drains have also been associated with reduced pain symptoms and faster recovery in patients undergoing thoracic surgery [2,23].

Early removal of chest drains has been shown to contribute to shorter hospital stays and better postoperative recovery [24]. Studies have even compared the use of urinary bladder catheters to chest drains and found that catheters resulted in shorter time to drain removal, reduced hospital stay, and improved wound healing [25].

Based on the these studies, small-bore drains have demonstrated safety in pre-clinical studies and in patients undergoing surgery for other thoracic conditions. Our hypothesis is that if a small-bore drain is safe and effective in treating pleural empyema, it should be more than sufficient for draining serous fluid and air leaks following a uniportal VATS lobectomy.

## Limitations

6

The purpose of this study is to examine safety in this specific patient population. In addition, the dataset generated during this trial should enable the sample size calculation for a subsequent feasibility trial. The limitations of this trial mainly result from the monocentric character of our study. This could limit the generalisability of our findings. Furthermore, we intentionally decided to include a patient cohort consisting of both patients with primary lung cancer and metastatic disease in order to face the current practice in thoracic surgery. Due to the nature of this trial we were not able to stratify for lung function. This could theoretically lead to an unbalanced distribution of patients with regards to lung function between the two groups. However, we are planning to address this issues upon completion of the trial and take them into consideration during the planning phase of the following trial.

## Potential benefits of the trial

7

As reported above, this is a phase I trial. It is only designed to prove safety and allow the sample size calculation for a following trial. During this trial we are planning to collect primary data on postoperative pain for patients undergoing anatomic lung resections. If the results of this trial confirm the safety of the smaller drains and suggest lower pain scores in the intervention group we would perform a further, large scale trial with this endpoint. Resolving the postoperative pain issue is one of the biggest challenges in modern thoracic surgery. This phase I trial could be the first step towards solving it.

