**Discussion:**

Thoracic surgery is becoming more and more minimally invasive. One of the remaining unresolved problems is postoperative pain, with the intercostal drain being one of the main contributing factors. Previous data from other studies suggest that the use of small-bore drains can reduce pain and speed up recovery without an increase in drain-related complications. However, no studies have been conducted on patients undergoing anatomic lung resections to date. The initial step in transitioning from larger to smaller drains is to establish the safety of this approach, which is the primary objective of this trial.

Trial registration: The study has been registered in the German Clinical Trials Register.

Registration number: DRKS00029982.

URL: https://drks.de/search/de/trial/DRKS00029982.

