We therefore consider it vital to address this issue in a formal trial. The aim of this phase I trial is to establish the safety of using a small-bore drain in these procedures and gain more insight on the effect of smaller drains on postoperative pain following thoracoscopic anatomic lung resections.

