### Study participants

2.1

A total of 40 patients undergoing uniportal video-assisted thoracoscopic lobectomy (uVATS) at the Center for Thoracic Diseases (CTD) will be recruited for this study. Patients meeting the inclusion criteria and providing informed consent will be enrolled. The sample size of 40 patients would allow us to analyze 20 patients on every group. This number is considered appropriate for Phase I trials in order to collect the necessary safety information and perform subsequent sample size calculations for a larger efficacy trial. In order to analyze 40 patients and taking into account the increasing number of anatomic segmentectomies performed and our conversion rate, we assume that around 100 patients need to be screened (Fig. 1).

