### Exclusion criteria

2.3

Patients who do not undergo lobectomy using minimally invasive techniques, and patients undergoing other types of lung resection (wedge resection, segmentectomy, bilobectomy/pneumonectomy) will be excluded. Patients with a history of congenital or acquired coagulopathy, use of direct oral anticoagulants, deviation from standard postoperative pain management regimen, or chronic analgesic therapy will also be excluded.

The study will randomize the 40 patients into two groups of equal size. Group 1 (control group) will consist of 20 patients who will receive a conventional 24 French (24F) chest drain according to current standards. In Group 2, a 14 French (14F) drain will be used (intervention group), which will be placed intraoperatively through the same access required for lung resection. The 14F drain will be secured to the skin with a separate suture, following the same technique as the placement of the 24F drain.

Drain removal is indicated by a board certified thoracic surgeon during the morning round on every postoperative day. In order for the drain to be removed there must not be any air leak during the past 24 h before the morning ward round and the fluid drainage has to be less than 5 ml/kg/24 h [14].

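### The article says the trial will establish, prove or confirm safety, but 20 patients per arm analysed descriptively can only give a preliminary estimate of the complication rate

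*Protocol article*

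**What the plan says.** Three places in the protocol article use strong wording about safety.

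- Abstract, Discussion paragraph (the final noun, cut here, is the trial itself): "The initial step in transitioning from larger to smaller drains is to establish the safety of this approach, which is the primary objective of this".
- Section 1, Background: "The aim of this phase I trial is to establish the safety of using a small-bore drain in these procedures".
- Section 7, Potential benefits of the trial: "It is only designed to prove safety and allow the sample size calculation for a following trial". The same section makes the large follow-on trial with a pain endpoint conditional on how the 14F arm fares: "If the results of this trial confirm the safety of the smaller drains and suggest lower pain scores".

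Other places are more modest. Section 2.1 gives the size, "The sample size of 40 patients would allow us to analyze 20 patients on every group", and its only justification, with a later efficacy study in view: "This number is considered appropriate for Phase I trials in order to collect the necessary safety information and perform subsequent sample size calculations". Section 6, Limitations, speaks only of examining safety, and does not list the sample size as a limitation. Section 4.3, Biometry, plans descriptive statistics followed by exploratory comparisons. It and the Abstract's Methods paragraph leave non-inferiority on complications to a later study; the power of 0.8 in the Abstract belongs to that study.

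The one numerical safety criterion is in section 4.2: the study is discontinued if the rate of complications or renewed drainage exceeds 20% among the first ten experimental subjects. No acceptable complication rate, margin or precision is given for the end of the trial.

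**The concern.** To establish or confirm safety means to rule out an unacceptable rate or an unacceptable excess over the standard drain. That needs a stated limit and enough patients for the interval to fall inside it. The article has neither, and elsewhere it defers this very comparison to a later study. The strong and the modest descriptions of the trial therefore conflict.

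The wording matters because it carries a decision. Confirmed safety is one of two conditions for a large trial whose endpoint would be pain, and the article does not say what result would count as confirmation.

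**Working it through.** **Plan's own figure.** Section 2.3 says "The study will randomize the 40 patients into two groups of equal size", so 2 × 20 = 40, which agrees with section 2.1. There is no further derivation to reproduce: no alpha, margin, expected composite rate or precision target is stated.

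**Inputs.** n = 20 per arm (section 2.1). The only event rates in the article are in section 5: "Statistically, the risk of obstruction is reported to be 8.1" per cent with small-bore drains, against 5.2% with large-lumen drains. These are for obstruction alone, from a cited study. The rate of the composite primary outcome (section 3.1) is not given, so steps 3 and 4 use 5.2% for 24F as an assumption. Steps 1 and 2 do not depend on it.

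**1. One-arm precision (exact Clopper-Pearson, two-sided 95%).** The upper limit p solves P(X ≤ x | 20, p) = 0.025. For x = 0 this is 1 − 0.025^(1/20) = 16.8%.

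| 14F events | Upper limit |
|---|---|
| 0/20 | 16.8% |
| 1/20 | 24.9% |
| 2/20 | 31.7% |

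For scale, 16.8 / 5.2 = 3.2 and 16.8 / 8.1 = 2.1.

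**2. Difference between arms (Newcombe 95%).** With 0 v 0, each arm's Wilson upper limit is z²/(n + z²) = 3.84/23.84 = 16.1%, so the interval is −16.1 to +16.1 points. With 1 v 1 it is ±19.1 points. With 2 on 14F and 1 on 24F it is −15.0 to +25.5 points.

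**3. Chance of a significant result.** Expected events at the cited rates are 20 × 0.052 = 1.04 and 20 × 0.081 = 1.62. Exact power is the sum of Bin(i; 20, 0.052) × Bin(j; 20, p14) over all pairs (i, j) with a two-sided Fisher P ≤ 0.05. With no events on 24F, five are needed on 14F. Fisher's test is my choice; section 4.3 names no test for the binary endpoint.

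**4. Adding the stopping rule.** More than 20% of ten is read as 3 or more of 10, and the same event rate is assumed for the rule and the primary outcome. P(stop) = P(X ≥ 3 | 10, p14). The last column is P(stop) + P(no stop and a significant excess at 20 per arm).

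| True 14F rate (24F 5.2%) | Fisher power | P(stop) | Stop or significant excess |
|---|---|---|---|
| 8.1% | 0.7% | 4% | 4% |
| 15% | 7% | 18% | 20% |
| 20% | 16% | 32% | 37% |
| 30% | 44% | 62% | 70% |

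**5. Sensitivity to the baseline.** A higher 24F rate does not help: at 10% v 20%, Fisher power is 7%.

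**6. What 20 per arm would support.** For non-inferiority with equal true rates of 5.2%, one-sided 0.025 and 80% power, the margin is (1.96 + 0.84) × √(2 × 0.052 × 0.948 / 20) = 2.80 × 0.0702 = 19.7 points. That means excluding only a rise from 5.2% to 24.9%. This is for orientation, since the article sets no margin.

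**The case against.** A 40-patient pilot that informs a later sample size is an ordinary design. Section 2.1 states that purpose, section 4.3 labels the comparisons exploratory, and the non-inferiority test is openly deferred. This stands, and it is why the point concerns the stated aim and not the number of patients.

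The stopping rule is a real numerical safeguard. Quoting Fisher power alone would suggest that a true 14F rate of 20% is missed about 84% of the time. That describes one test, not the trial: with the rule, the chance of a stop or a significant excess is about 37%. The rule still covers only the first ten experimental patients, and at a true rate of 15% to 20% it triggers in only 18% to 32% of trials. Passing it does not show safety.

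A reader might infer that safety would be declared by default from a non-significant test, so that harm would most likely be read as safety. The article does not say so. Its first analysis is descriptive, and at 20% v 5.2% the 14F arm would show more events than the 24F arm about 89% of the time, so a plain report would usually display the excess. What remains is that no criterion is given for calling safety confirmed.

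The 5.2% and 8.1% are obstruction rates, not composite rates. This too stands; the fold-increases and the power figures are conditional on that proxy.

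A separate analysis plan may hold more detail, but it could not alter the precision that 20 patients per arm provide.

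**Conclusion.** The point holds as a mismatch between the stated aim and what the design can deliver. The Abstract, section 1 and section 7 promise to establish, prove or confirm safety. The best possible result, 0/20 on 14F, still leaves rates up to 16.8% open, and 0 v 0 leaves a difference of about 16 points open. These two figures rest only on n = 20 per arm and standard 95% intervals. The detection figures (37% at a true 20%, 70% at 30%, stopping rule included) also assume 5.2% for the 24F composite, Fisher's test, and the stopping rule read as 3 or more of ten.

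The sample size, the endpoint and the exploratory analysis need not change for this point. It should be corrected because confirmed safety is a condition for the next trial.

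**What to change.** 1. In the Abstract's Discussion paragraph, section 1 and section 7, replace the wording about establishing, proving or confirming safety with: *obtain a preliminary estimate of the drain-related complication rate with its 95% confidence interval*. This matches the modest wording already in sections 2.1 and 6.
2. In section 2.1, state the precision at 20 per arm: upper 95% limits of 16.8%, 24.9% and 31.7% for 0, 1 and 2 events, and about ±16 points for 0 v 0.
3. In section 6, add the sample size to the limitations.
4. In section 4.3, state that a non-significant difference between the groups is not evidence of safety.
5. In section 7, make the condition for the next trial refer to the estimate and its interval. Any numerical limit is for the sponsor to set, and would be a new decision rule, not just a wording change. With 20 patients the upper two-sided 95% limit cannot fall below 16.8%, so a stricter limit on that bound could never be met.

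Items 1 to 4 are text changes. None of the five needs extra patients. The cost is a more modest stated conclusion.

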## Ethics approval and consent to participate

All methods were carried out in accordance with relevant guidelines and regulations and approved by the district medical council of Rhineland-Palatinate (Approval Nr. 2021–15994). Informed consent will be obtained from all subjects and/or their legal guardian(s).

## Consent for publication

Not Applicable.

## Availability of data and materials

This paper here presents the trial protocol and there are therefore no datasets to make available for further use. The raw data that will be collected during this trial will be subject of a second publication in the future.

## List of abbreviations

F: French
CTD: Center for Thoracic Disease
VATS: video-assisted thoracoscopic surgery
BMI: body-mass index
NAS: numerical analog scale
ERAS: enhancement recovery after surgery
FEV1: forced expirium volume in the first second
